## Methods

### Ethics Approval and Consent to Participate

This study will comply with relevant ethical regulations as outlined and approved by the Indiana University Institutional Review Board (16141) on August 2, 2022. Informed consent will be obtained from participants using electronic agreement to a study information sheet embedded at the beginning of the experiment. Participants will be paid US $1.50 on the successful completion of the study and submission for compensation (see Sampling Plan).

### Design

#### Trial Design

We will conduct a randomized controlled trial consisting of 2 parallel groups and a 1:1 allocation ratio. Our planned study workflow is provided in Figure 1. Allocation will be automated by the Randomizer feature in the QualtricsXM platform [33] and thus, by definition, will be concealed from researchers until after each case has been assigned. However, we note that based on our prior experience, the use of data quality checks and the 2-step survey completion procedures in the Prolific platform can result in unbalanced allocation for a very small portion of the sample as recruitment approaches the planned limit (eg, if the number of usable surveys exceeds the number of surveys solicited, the excess surveys may not be allocated 1:1 but will still be included following sensitivity analysis) [20].

This study will be, in principle, a double-blind study; participants will be unaware that they are being randomized to a condition, and allocation will be done exclusively by software. However, analysts will not be blinded to the meaning of the group assignment variable.

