#### Statistical Analyses

Descriptive statistics of demographics and outcomes will be calculated. We will explore distributions of trust in science (Hypothesis 1) and each of the single-item measures (Hypotheses 2-5).

Data will be analyzed using analysis of covariance (ANCOVA), with the assignment of the study arm (intervention vs control) used as the independent variable and the specified outcomes (depending on the hypothesis) set as the dependent variable. All specified covariates will be included in each model, and assumptions for the analyses will be evaluated (eg, the normality of residuals and linear relationships between covariates and the dependent variable). If assumptions are not met, the research team will explore different transformations or nonparametric models as recommended by statistical experts.

Missingness is not anticipated owing to the study design, but if it occurs at a meaningful level (>5%), we will perform sensitivity analysis using Multiple Imputation by Chained Equations to explore how missingness affects the results, and in the case that the results differ, we will report Multiple Imputation by Chained Equations as the primary analysis.

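### Unblinded analysts may pick an unspecified fallback model after seeing the data; the model for each outcome should be locked before any arm contrast is produced

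*Protocol article*

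**What the plan says.** - **Blinding (Trial Design).** "This study will be, in principle, a double-blind study", explained by participants not knowing that they are randomized and by software allocation. The same paragraph then discloses that "analysts will not be blinded to the meaning of the group assignment variable".
- **Primary model (Statistical Analyses).** "Data will be analyzed using analysis of covariance (ANCOVA), with the assignment of the study arm (intervention vs control) used as the independent variable". "All specified covariates will be included in each model, and assumptions for the analyses will be evaluated". The checks given as examples are normality of residuals and linearity between covariates and outcome.
- **Fallback (Statistical Analyses).** "If assumptions are not met, the research team will explore different transformations or nonparametric models as recommended by statistical experts".
- **Missing data (Statistical Analyses).** Multiple imputation is run if missingness exceeds 5%, and "in the case that the results differ, we will report Multiple Imputation by Chained Equations as the primary analysis".
- **Outcomes and hypotheses.** Hypothesis 1 uses a 21-item scale; Hypotheses 2 to 5 use single 7-point items (Primary Outcomes). All five predict lower values in the intervention arm, but the tests are two-tailed, and Table 1 counts a significant result in either direction as evidence.

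**The concern.** The document does more than leave a detail unstated. It fixes two things together: the analysts know the arms, and the same team searches among alternative models once the data are in hand. Nothing says when an assumption has failed, which alternative comes first, or that the choice is made before the arm effect is seen. An analyst could therefore fit several defensible models, see which supports the prediction, and report that one without breaking any written rule.

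The branch could well be reached. Four of the five outcomes are single bounded 7-point items, and normality of residuals is a listed check. At stake are the stated error levels of .05 and .01 and the strength of the preregistration. The band .01<P<.05, where the protocol promises a balanced interpretation, is where a change of model most easily moves a result.

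**Working it through.** **1. The plan's own figure.** Inputs from Sample Size Determination and Power Analysis: N=1500, 1:1, so 750 per arm; 80% power; two-tailed.

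Detectable d = (z(1−α/2) + z(0.80)) × √(2/750)
- α=.05: 0.1447, stated as 0.14
- α=.01: 0.1765, stated as 0.18

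Both reproduce after rounding. They presuppose one fixed test per outcome.

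**2. Is the fallback a remote contingency?** With 750 per arm and no covariates, a Shapiro-Wilk test at .05 rejected normality in 500 of 500 simulated data sets, for a skewed and for a symmetric 7-point item. The protocol names no test and covariates would smooth the residuals, so this shows only that the branch is plausible.

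**3. What open choice costs under no effect.** The documents give no item distribution, so two were assumed for scores 1 to 7, with 750 per arm and no covariates:
- Item A: .03, .04, .06, .12, .25, .30, .20 (4,000 replicates, run twice)
- Item B: .05, .04, .06, .12, .18, .30, .25 (10,000 replicates)

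A false positive is counted if any analysis on the menu is significant.

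| Item and menu | two-sided .05 | two-sided .01 |
|---|---|---|
| A: raw only | 5.1% | 0.9% (repeat 0.95%) |
| A: raw, reflected log, square, rank | 7.1% (repeat 7.1%) | 1.2% (repeat 1.4%) |
| B: raw only | 4.99% | 0.86% |
| B: raw or rank | 6.42% | 1.17% |
| B: raw, reflected log, square, rank, reflected square root | 6.58% | 1.23% |

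Monte Carlo standard errors: √(.05×.95/10,000) = 0.22 percentage points for item B at 5%; √(.071×.929/4,000) = 0.41 points for item A at 7.1%; √(.012×.988/4,000) = 0.17 points for item A at 1.2%. The 1.2% and 1.4% are not distinguishable.

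The rise at .05 is 6.42 − 4.99 = 1.43 points at the low end and 7.1 − 5.1 = 2.0 points at the high end. It is small because the candidate analyses are highly correlated.

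**4. Selection in the predicted direction only (item B).** At nominal .05 the error rises from 2.53% to 3.27–3.34%; at .01, from 0.39% to 0.54–0.56%.

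**5. Would an A/B label be enough?** No. The two-sided figures in step 3 require no knowledge of which arm is which. An analyst who sees A against B and may still choose the model keeps the 6.4–6.6% at .05 and 1.2% at .01 found for item B. The nominal level returns only if the model is fixed without sight of the contrast.

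**6. Can the checks be run without the arm?** Yes. Both named checks concern residuals and covariate–outcome relations. Omitting the arm term at the stated d=0.18 adds (0.18/2)² = 0.0081, about 0.8% of the within-arm variance, so it hardly alters the residual shape.

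**The case against.** **The primary analysis is locked.** ANCOVA, the five outcomes and the covariates are fixed, and the fallback opens only on assumption failure. This stands, and it caps the harm. The simulation ignores that gate and assumes unrestricted selection, so it is an upper case.

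**Fallback detail belongs in an analysis plan or registration not shown here.** Fair as to detail: a missing ranked list in a condensed article would be no finding by itself. What remains is the stated combination of unblinded analysts and an exploratory model search.

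**The simulation measures open model choice, not unblinding.** Correct. Knowing the labels adds only the chance to select in the predicted direction (step 4 of the working).

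**Safeguards exist.** Tests are two-tailed and read in either direction, exact P values are promised, and raw data and code will be published. These let readers detect a selective choice afterwards; they do not prevent it.

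Four stronger readings are tempting, and the documents do not support them:
- *The blinding statement contradicts itself.* It is qualified, explained and followed by an open disclosure of the analyst exception.
- *The status of imputed results is a free choice.* The 5% trigger and the direction of the switch are fixed. Only the meaning of differing results is undefined, and forced responses (Participants and Procedures) make the branch unlikely.
- *Handling of excess surveys is left open.* Trial Design says that "excess surveys may not be allocated 1:1 but will still be included following sensitivity analysis", and Technical Exclusion and Inclusion Procedures says that completers who do not request payment are analyzed as assigned.
- *Inflation is larger because items could be dichotomized.* The plan names only transformations and nonparametric models.

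**Conclusion.** The point holds in limited form. Analysts who know the arms may choose an unspecified transformation or nonparametric model after seeing the data, so the fallback could follow the arm result. In the worst case, the per-outcome two-sided type I error moves from about 5% to 6.4–7.1% at .05, and from about 0.9% to 1.2–1.4% at .01. These figures rest on assumed skewed 7-point items, no covariates, no true effect and free selection across the menu; they do not describe the 21-item scale of Hypothesis 1. This is a moderate weakness that should be repaired, not a flaw that invalidates the design. A reader might infer that masking the arm label alone would remove the problem. It would not, because the A-versus-B contrast would remain visible and significance in either direction counts.

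**What to change.** Replace the analyst sentence in Trial Design and the fallback sentence in Statistical Analyses with a rule to this effect:

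1. At export, split off the arm variable and every field that reveals it, including the second comprehension item, which only the intervention arm sees.
2. Before any arm contrast is produced, carry out the assumption checks on pooled data or on residuals from models without the arm term, against criteria written in advance.
3. Name one ordered fallback per outcome type in advance. Fix and date the model for each outcome in a log, then merge the arm variable back. Any diagnostic that needs the arm is reported afterwards and does not reopen the choice.
4. Always report the planned ANCOVA beside any fallback.
5. If missingness exceeds 5%, report the imputed result beside the complete-case result, instead of switching on an undefined difference.

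The cost is a small data-preparation step, by a team member or a script, plus a few sentences in the registration. N stays at 1500, and the detectable effects stay at 0.1447 and 0.1765. The Results section says that the protocol was submitted before any recruitment, so the change could be made in time.

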**Figure 1 figure1:**
[figure not shown]
Study design and workflow.

#### Participants and Procedures

This study will solicit participants (n=1500) from the Prolific crowdsourced US representative participant pool, which provides a cross-section of age, sex, and race/ethnicity that mirrors the national US population [34]. This sampling frame also provides the de facto eligibility criteria of being aged ≥18 years and residing in the United States. Studies have found the Prolific platform to produce high-quality research data in general and relative to competing services (eg, Qualtrics and Dynata panels, Amazon MTurk, and CloudResearch) [35,36].

When individuals indicate interest in participating in the study, they will be provided with a link to the experiment, which will be hosted on the QualtricsXM platform. Participants who agree to participate in the study (study information sheet) will complete the first block of questions, which will include sociodemographic items intermixed with screening questions to identify the risk of low-quality data (ie, virtual private network or bot use, inattention, and dishonesty) [37]. Individuals who fail 1 or more checks will be considered ineligible for the study and asked to return the study to the Prolific platform for reselection.

As noted in Figure 1, randomization will occur after all determinations of eligibility to preserve sample composition and allocation. The study will be fully insular (eg, all components occur within the QualtricsXM platform and within 1 “sitting”). To mitigate the potential impact of missing data, participants will not be permitted to advance the survey if they have not answered all questions on a given page. All data will be exported directly from the QualtricsXM platform to a local data file once the study closes, and the code used for data cleaning (see Sampling Plan) will be shared alongside the raw data.

#### Intervention and Control Description

To isolate the specific effects of normative language in describing scientific findings, we will show participants 1 of 2 fake social media posts depending on the study arm to which they are randomized. The posts will be identical except for the inclusion of normative language in the intervention post. To improve ecological validity [38], both posts will be designed using the formatting parameters for modern Facebook timeline posts as displayed in a web browser using “night” mode (see Figures 2 and 3). The posts will appear as posts “Suggested for you” from a generic science page, which is the primary subheading that Facebook uses when inserting content that is not explicitly followed on a person’s timeline. The lead-in text will read, “Today’s post highlights a study published back in April 2020, right after the COVID-19 pandemic arrived in the United States. This was from a peer-reviewed paper in *Infectious Disease Modeling*.” Both posts will be accompanied by the same generic image of a surgical face mask and a bottle of hand sanitizer.

Additionally, in service of ecological validity, the written content of the graphics will be drawn directly from a highly cited April 2020 paper on face masks for the prospective prevention of COVID-19 [39]. The control post (Figure 2) will feature only a cognitive claim: “Scientists used models based on data from New York and Washington. Their results showed that ‘broad adoption of even relatively ineffective face masks may meaningfully reduce community transmission of COVID-19 and decrease peak hospitalizations and deaths.’”

The intervention post (Figure 3) will include the same cognitive language but also add a normative statement derived from the same source paper. It will add “Based on their findings, the study authors suggested ‘that face mask use should be as nearly universal (i.e., nation-wide) as possible and implemented without delay, even if most masks are homemade and of relatively low quality.’”

**Figure 2 figure2:**
[figure not shown]
Control image.

**Figure 3 figure3:**
[figure not shown]
Intervention image.

Once the image is displayed, participants will not be able to advance the survey for at least 30 seconds (the button to continue the survey will be linked to a timer). A message indicating this delay will be provided on the screen. After participants advance, they will transition to a screen featuring a smaller copy of the image appropriate for their study arm, along with 1 (control) or 2 (intervention) comprehension questions.

Both arms: (True/False) “In the social media post you read about a scientific study from April 2020, the study authors found that face masks could reduce the spread of COVID-19 as well as lowering hospitalizations and deaths.”Intervention arm only: (True/False) “In the social media post you read about a scientific study from April 2020, the study authors recommended that everyone in the US should start wearing masks immediately.”

Any response other than “True” for either question will display a message asking the participant to read the post carefully again, and then participants will be returned to the social media post (no 30-second delay on subsequent viewings), from which they can proceed forward to the comprehension questions again.

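### Only the intervention arm answers a second comprehension item that restates the recommendation more firmly than the post, so the arm contrast is the post plus that check

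*Protocol article*

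**What the plan says.** All of this is in the protocol article, mostly under Intervention and Control Description.

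- The aim: "To isolate the specific effects of normative language in describing scientific findings, we will show participants 1 of 2 fake social media posts". The means: "The posts will be identical except for the inclusion of normative language in the intervention post".
- The intervention post adds a sentence, introduced by the verb *suggested*, which reads in part: "that face mask use should be as nearly universal (i.e., nation-wide) as possible and implemented without delay, even if most masks are homemade". Its remaining words concede that masks may be of low quality.
- After at least 30 seconds on the post, participants move to a screen with a smaller copy of it, "along with 1 (control) or 2 (intervention) comprehension questions". Both arms get the same true/false item on the modelling result. Only the intervention arm gets a second one, stating that "the study authors recommended that everyone in the US should start wearing masks immediately".
- The rule for a wrong answer follows: "Any response other than “True” for either question will display a message asking the participant to read the post carefully again". The participant then goes back to the post, this time without the 30-second minimum.
- Table 1 reads a significant difference on any of the five outcomes, in either direction, as caused by the inclusion of normative language.
- Limitations mentions the comprehension checks only in connection with whether participants engage enough with the content. It does not mention that the checks differ by arm.

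**The concern.** The purpose of two posts that match except for one sentence is to let any difference be credited to that sentence. The protocol controls the posts carefully and then adds a step in which the arms differ again. Intervention participants read the recommendation a second time, in the investigators' wording, and must mark it True to go on. Control participants have no corresponding second item.

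The shared cognitive item is also a paraphrase, but it is the same in both arms and cancels. The recommendation item does not cancel. It also attributes a firmer demand to the study authors, and Hypothesis 2 then asks how credible the scientist who conducted the study is.

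What is at stake is attribution. A finding could be reported as the effect of how scientists phrase their results when part of it came from how the survey phrased its check. Every intervention participant receives both, so no later analysis can separate them.

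**Working it through.** **1. The two wordings compared**

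| Element | Post | Intervention-only item | Change |
|---|---|---|---|
| Verb | suggested | recommended | firmer |
| Scope | as close to universal as possible, nation-wide | everyone in the US | from nearly all to all |
| Timing | without delay | immediately | little or none |
| Mask quality | concedes homemade, low-quality masks | absent | qualifier dropped |

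The item is firmer in verb and scope and loses a qualifier. The change in timing is negligible.

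**2. Does the check come before the outcomes?** No single sentence says so, and the workflow figure is not available in the text reviewed. The Methods paragraph of the Abstract makes verifying understanding part of what happens in each arm. The check follows directly after the post, and the items for Hypotheses 2 to 5 ask about the post and study just read. Check first, outcomes second is the only sensible reading, but it is an inference.

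**3. What the arms differ by.** Intervention minus control = the normative sentence in the post + one extra item in firmer wording + one extra route back to the post. Only the first term is what the protocol sets out to isolate.

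**4. The plan's own detectable effects.** Inputs from Sample Size Determination and Power Analysis: 1500 participants, equal allocation (750 per arm), 80% power, two-tailed, α=.05 and corrected α=.01.

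Detectable d = (z(1−α/2) + z(0.80)) × √(2/750), with √(2/750) = 0.0516.

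- α=.05: (1.960 + 0.842) × 0.0516 = 0.145
- α=.01: (2.576 + 0.842) × 0.0516 = 0.176

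These agree with the stated 0.14 and 0.18.

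**5. How much a small effect of the check could matter.** The documents give no size for such an effect, so b below is an assumption. Suppose the post's sentence has no effect and the extra item alone shifts an outcome by b SD. The chance of a significant arm difference is Φ(b/0.0516 − z(1−α/2)) + Φ(−b/0.0516 − z(1−α/2)), without covariate adjustment:

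| b (SD) | α=.05 | α=.01 |
|---|---|---|
| 0.02 | 6.7% | 1.6% |
| 0.05 | 16% | 5.4% |
| 0.10 | 49% | 26% |
| 0.14 | 77% | 55% |

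An effect of the check well below the detectable d would raise the false-attribution rate noticeably above the nominal level. An effect of 0.02 SD would hardly change it.

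**The case against.** The case on the other side has real weight.

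- **The text does not strictly contradict itself.** The statement that the posts are identical apart from normative language is about the posts, and it is true of them. Table 1 speaks of including normative language and does not say it must be in the post. The extra item is itself normative, so in a broad sense the contrast is still normative versus none. This stands. The gap lies between the aim of isolating the effect and a procedure that adds a second, differently worded stimulus.
- **The rewording is modest.** The post itself says nation-wide, which brings it closer to the item's scope. This stands in part: the shifts in verb and scope and the dropped qualifier remain.
- **Nobody is made to endorse masks.** A reader might infer forced agreement. The item asks what the study authors recommended, so answering True reports content and states no opinion.
- **Looping is probably minor.** A reader might infer that two items roughly double the re-exposure. That rests on failure rates the documents do not give, and on independent items with equal failure rates. Under those assumptions, failure rates of 2%, 5% or 10% per item give 1−(1−q)² = 4.0%, 9.8% or 19.0% looped in the intervention arm. The excess over control is 1.96, 4.75 or 9.0 percentage points. To move the arm mean by 0.14 SD, each additionally looped person would have to shift by 0.14/0.0196 = 7.1, 0.14/0.0475 = 2.9 or 0.14/0.09 = 1.6 SD. The post is also visible beside the questions, and repeat viewings carry no delay. Looping alone is therefore not a credible driver at the lower rates. The extra item, which everyone in the arm reads, is the main issue.
- **The check has a purpose.** It confirms that the manipulated sentence was read, and insufficient engagement is the first limitation the protocol names. This stands, and is a reason to keep the check before the outcomes.

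**Conclusion.** The point holds as a matter of attribution. Randomization is intact, and the arm difference is a valid estimate of the effect of the whole package: post, arm-specific reworded check and any rereading. It is not an estimate for the post's normative sentence alone, and the planned analyses cannot make it one.

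The size of the problem cannot be found from the documents. The figures for b are illustrations that matter because the trial is built to detect differences of about 0.14 to 0.18 SD. The conclusion also assumes that the check precedes the outcomes.

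A reader might go further and infer that the check biases results toward the hypothesised lower trust, for instance through irritation at being corrected. Nothing in the documents supports a direction, and repetition could as well raise acceptance. Nor do they support calling the comparison invalid. This is an inexpensive improvement that can only be made before data are collected.

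**What to change.** Keep the comprehension check before the outcomes and match it across arms:

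1. Word the intervention item verbatim from the post's own sentence.
2. Give control participants a second true/false item on content common to both posts, for example that the models used data from New York and Washington, so that both arms answer two items.
3. Record first-attempt answers and the number of returns to the post, and report them by arm.

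If the check is left unmatched, state the conclusion in Table 1 and the report as the effect of the post plus its comprehension check.

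The cost is minor survey reprogramming and one extra item for control participants. The Results section says the protocol was submitted before any recruitment, so the change was feasible at that stage. The normative sentence would still be repeated in the intervention arm, and this should be described as part of the exposure. Moving the recommendation item to after the outcomes would remove that repetition too, but would give up verified exposure before measurement. That trade-off is a reason to prefer matching.
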